## Abstract

**Background::**

Congenital heart disease in children with pulmonary hypertension is a common and serious complication, which has a direct impact on the surgical effect and prognosis of children. Bosentan and vardenafil are commonly used drugs for the treatment of postoperative pulmonary hypertension in children with congenital heart disease, and there are few clinical studies on their combined use. Therefore, the purpose of this randomized controlled trial is to evaluate the effectiveness and safety of the combined use of 2 drugs in the treatment of postoperative pulmonary hypertension in children with congenital heart disease.

**Methods::**

This is a prospective randomized controlled trial to study the effectiveness and safety of bosentan combined with vardenafil in the treatment of postoperative pulmonary hypertension in children with congenital heart disease. Approved by the clinical research ethics committee of our hospital. The patients were randomly divided into 1 of 2 treatment regimens:

Patients, doctors, nurses, and data collection assistants were blinded to group allocation. Observation indicators include: oxyhemoglobin saturation (SpO2), 6-min Walking Test Distance (6 MWTD), systolic pulmonary artery pressure, mean pulmonary artery pressure, Borg score, NYHAFC score, etc. Data were analyzed using the statistical software package SPSS version 25.0 (Chicago, IL).

**Discussion::**

This study will evaluate the effectiveness and safety of bosentan combined with vardenafil in the treatment of pulmonary hypertension after congenital heart disease in children. The results of this experiment will provide a clinical basis for the use of bosentan combined with vardenafil to treat pulmonary hypertension after congenital heart disease in children.

**Ethics and dissemination::**

Private information from individuals will not be published. This systematic review also does not involve endangering participant rights. Ethical approval was not required. The results may be published in a peer-reviewed journal or disseminated at relevant conferences.

**OSF Registration number::**

DOI 10.17605/OSF.IO/962BT.

## Introduction

1

Congenital heart disease (CHD) refers to vascular or heart malformations caused by abnormal growth of cardiac blood vessels during the embryonic period. It is a common cardiovascular disease in pediatrics,^[1]^ due to the large amount of left to right shunts at the defect site of CHD. The blood volume of the pulmonary circulation increases significantly, and the high flow puts the pulmonary blood vessels in a state of high pressure and high resistance, causing pulmonary arterial hypertension. Pulmonary hypertension is one of the common and serious complications of congenital heart disease in children. About 10% of children with congenital heart disease develop into PAH,^[2]^ which can occur at various stages in the evolution of congenital heart disease in children. The surgical effect and prognosis of patients have a direct impact, and the perioperative mortality rate of children with CHD and severe PAH is higher.^[3]^ Therefore, effectively reducing pulmonary hypertension is a key step to improve the surgical efficacy and quality of life of CHD patients.

There are currently 3 types of targeted therapy drugs recommended, including endothelin receptor antagonists, prostaglandin i2, and phosphodiesterase 5 inhibitors (PDE-5 inhibitors).^[4]^ Bosentan is a representative drug of endothelin receptor antagonists, which has the effects of reducing pulmonary vascular resistance, improving hemodynamic indicators, improving exercise tolerance, and improving the patient's survival rates.^[5,6]^ Vardenafil is a highly selective inhibitor of phosphodiesterase-5 (PDE-5), which can selectively inhibit PDE-5 activity and reduce the degradation of cyclic guanosine monophosphate (cGMP). The latter can further activate protein kinase G, increase potassium ion channels, reduce calcium ion concentration, thereby reducing pulmonary artery pressure. At present, clinical studies have pointed out that the two-drug combination therapy can significantly improve the patient's exercise capacity, improve the patient's heart function and relieve the symptoms of dyspnea,^[7]^ but there are too few similar studies, and the sample size is not large, and it is difficult to draw reliable conclusions. Therefore, the purpose of this randomized controlled trial is to evaluate the effectiveness and safety of bosentan combined with vardenafil in the treatment of postoperative pulmonary hypertension in children with congenital heart disease.

## Materials and methods

2

### Study design

2.1

This is a prospective randomized controlled trial to study the effectiveness and safety of bosentan combined with vardenafil in the treatment of postoperative pulmonary hypertension in children with congenital heart disease. We followed the Consolidated Standards of Reporting Trials (CONSORT) guidelines for reporting randomized trials and provided a CONSORT flow diagram (Fig. 1) and the Standard Protocol Items: Recommendations for Interventional Trials (SPIRIT) 2013 statement.

**Figure 1 F1:**
[figure not shown]
Flow diagram.

### Ethics and registration

2.2

This research program is in accordance with the Helsinki Declaration and approved by the Clinical Research Ethics Committee of our hospital. This protocol has been registered in open Science Framework (OSF) (Registration number: DOI 10.17605/OSF.IO/962BT). All patients need to sign a written informed consent before they are randomly assigned to continue the trial.

### Sample size

2.3

The calculation of the sample size is based on the results of the 6 MWTD. According to the results of the pre-test, the average score of the experimental group is estimated to be 495.47 and the standard deviation is 54.72. The control group averaged 456.33 and the standard deviation was 54.68. The sample size calculation formula is as follows$$n=n1=n2=\frac{{\left(u_{\alpha }+u_{\beta }\right)}^{2}\times \sigma^{2}}{\delta^{2}}\times 2$$

At the 5% significance level, a total of 34 patients are required for each group to achieve 90% power. The estimated withdrawal rate is 20%, and 42 patients will be included in each group.

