### Study design

2.5

Eligible participants were randomly assigned to the treatment group or control group at a ratio of 1:1 using a random tool based on the central network. Randomization was performed without any stratification using SAS 9.3 software (SAS Institute, Cary, NC, USA) by independent statisticians who were not involved in the implementation of the experiment or statistical analysis. Randomization was performed without any stratification. The clinical research coordinator enters participant information on the tablet and is given a random number. The research assistant gets the participant's assignment from the computer. Throughout the research process, the research assistant is responsible for screening, recruiting participants, and assigning random numbers to the included participants. The result assessor is responsible for the assessment of the scale. All bed doctors, researchers, research assistants, participants, intervention supervisors, and statisticians who perform statistical analysis are unknowable in the grouping of personnel.

The dispensation of medicines will be assigned to patients with corresponding numbers by unknowing nurses according to the medicine numbers.

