### Statistical analysis

2.9

Data were analyzed using the statistical software package SPSS version 25.0 (Chicago, IL). Continuous variables were described as the mean ± standard deviation, and differences between groups were analyzed using a series of one-way analysis of variance (ANOVA) with Bonferroni posthoc test, while differences between groups over time were analyzed using multiway ANOVA with Bonferroni posthoc test. Categorical variables were described as the number (%), and were analyzed by Fisher exact test. A *P* value of <.05 was considered statistically significant.

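### The 34 per group stated for 90% power follows only from a one-sided 5% critical value; the planned ANOVA at P<.05 is two-sided in effect and has about 82–83% power at 33–34 evaluable per group

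*Protocol article*

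**What the plan says.** Section 2.3 (Sample size) names the sizing outcome: "The calculation of the sample size is based on the results of the 6 MWTD". From a pre-test, "the average score of the experimental group is estimated to be 495.47 and the standard deviation is 54.72", and "The control group averaged 456.33 and the standard deviation was 54.68". It prints the standard formula for comparing two means, with u_α + u_β in the numerator, and does not say whether u_α is a one-sided or a two-sided critical value. The result is "At the 5% significance level, a total of 34 patients are required for each group to achieve 90% power", followed by "The estimated withdrawal rate is 20%, and 42 patients will be included in each group".

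Section 2.5 (Study design) gives equal allocation: "Eligible participants were randomly assigned to the treatment group or control group at a ratio of 1:1".

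Section 2.9 (Statistical analysis) names the test for continuous variables: "differences between groups were analyzed using a series of one-way analysis of variance (ANOVA) with Bonferroni posthoc test". Its threshold is a P "value of <.05 was considered statistically significant". Neither section uses the words one-sided or two-sided.

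**The concern.** The inputs, formula, significance level, power and answer are all printed, so the sample size can be checked in full. The answer of 34 matches a one-sided critical value, but the test named in 2.9 is non-directional. The trial would then be sized for one test and analysed with another.

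The stated 90% power is the justification for the number of children enrolled. If the planned test has less power than that, the risk of missing the assumed effect is understated, and a non-significant result would be read against a power that the trial did not have.

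**Working it through.** **Inputs (section 2.3).**
- Means 495.47 and 456.33, so δ = 495.47 − 456.33 = 39.14. The section gives no unit; metres are assumed, as for a walking distance.
- SDs 54.72 and 54.68, so σ = √[(54.72² + 54.68²)/2] = 54.70.
- Standardised difference δ/σ = 39.14/54.70 = 0.7155.
- α = 0.05, power 90% (u_β = 1.2816), equal groups (section 2.5), withdrawal 20%.

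**Step 1: reproduce the plan's figure with its own formula.** n per group = 2 (u_α + u_β)² σ²/δ², where 2σ²/δ² = 2 × 54.70²/39.14² = 3.906.
- One-sided 5%: (1.645 + 1.2816)² × 3.906 = 33.45, rounded up to **34**, the stated number.
- Two-sided 5%: (1.960 + 1.2816)² × 3.906 = 41.04, rounded up to **42**.

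Two-sided 5% with lower power does not give 34 either: 80% gives 31 and 85% gives 36.

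**Step 2: what the planned test is.** In a one-way ANOVA of two groups, F is the square of the t statistic. Comparing its P value with .05 is therefore the same as a two-sided t test at 5%. With only two groups the Bonferroni step has a single contrast and changes nothing.

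**Step 3: power of that test.** By normal approximation, power ≈ Φ(0.7155 × √(n/2) − 1.960). At n = 34 this is Φ(2.950 − 1.960) = Φ(0.990) = 83.9%. The noncentral t calculation, which matches the ANOVA, is a little lower:

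| Evaluable per group | Two-sided, t | Two-sided, normal | One-sided, normal |
|---|---|---|---|
| 33 | 81.7% | 82.8% | 89.6% |
| 34 | 82.8% | 83.9% | 90.4% |
| 42 | 89.98% | 90.6% | 94.9% |
| 43 | 90.7% | 91.3% | 95.3% |

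At 33–34 evaluable the two-sided type II error is between 100 − 83.9 = 16.1% and 100 − 81.7 = 18.3%.

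**Step 4: withdrawals.** 42 × 0.80 = 33.6, so about 33 or 34 per group remain. Keeping two-sided 90% after 20% withdrawal would take 42/0.8 = 52.5, so 53 enrolled per group by the formula, or 43/0.8 = 53.75, so 54 by noncentral t. The plan has 42.

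**Step 5: what baseline adjustment could recover.** ANCOVA replaces σ by σ√(1 − ρ²), with ρ the correlation between baseline and month 6. At 33 per group, two-sided 5% (noncentral t, one degree of freedom spent on the covariate):

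| Assumed ρ | Power |
|---|---|
| 0.30 | 85% |
| 0.40 | 88% |
| 0.47 | 90% |
| 0.50 | 91% |

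The document states no value of ρ. These figures also presume that the quoted SDs are unadjusted.

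**The case against.** **Sidedness is inferred.** Section 2.3 prints u_α and not u_{α/2}, and read one-sided it agrees with its own formula. A reader might therefore infer either that the sum in 2.3 is simply wrong or that the protocol declares a two-sided test. The document supports neither. What remains is a mismatch between a one-sided sizing and a non-directional analysis. The inference is sound, because the named ANOVA is two-sided in effect and no directional test appears anywhere. An unseen analysis plan does not remove the point, since both the sample size and the test are stated here.

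**Withdrawal arithmetic.** A reader might also infer an error in the step from 34 to 42, because 34/0.8 = 42.5 points to 43. That is only a rounding choice: the unrounded requirement gives 33.45/0.8 = 41.8, which rounds up to 42. It should not be raised.

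**The number evaluable is not known.** Section 2.4 admits children from just over 6 months of age, and section 2.7 restricts the walking test to children able to cooperate with it. A child who cannot do the walk has no value even without withdrawing, so 33 per group cannot be read off the 20% rate alone. This stands, and any restated power must be conditional on it.

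**The loss is moderate.** Power of about 82% is still above 80%. If nobody withdrew and all could do the walk, 42 per group would give about 90%. The type I error and the effect estimates are unaffected. All this is fair, but the stated 90% remains a figure that the planned test does not deliver under the plan's own withdrawal assumption.

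**Conclusion.** The point holds as a mismatch between sections 2.3 and 2.9. The gap between 34 and 42 is eight patients per group, about 24% of 34, and is too large to be rounding. Under the plan's own effect and SD, its own 20% withdrawal and the ANOVA it names, power is about 82–83% by the t calculation (at most 83.9% by normal approximation), and the risk of missing the assumed effect is about 16–18% rather than 10%.

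This rests on three assumptions: the ANOVA P value is used as printed, without a directional rule; the pre-test means and SDs are correct; and 33–34 children per group have a month-6 walking distance. If inability to do the walk reduces that number further, power is lower still. A reader might infer that baseline adjustment restores 90% without extra patients. The document does not support that as a fact, because it gives no correlation and section 2.7 does not say that walking distance is measured before treatment.

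**What to change.** Restate section 2.3 as: two-sided 5% level; 42 randomised per group; power of about 82% for a difference of 39.14 m with SD 54.7, provided that about 33 per group have a month-6 walking distance, and lower if children who cannot do the walk reduce that number.

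Alternatively, if one-sided testing was intended, declare it in both 2.3 and 2.9 and replace the ANOVA for walking distance with a named directional test.

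Optionally, analyse walking distance by ANCOVA adjusted for baseline, if it is measured at baseline. Present the gain as conditional on an assumed correlation, over the range 0.3 to 0.5.

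The restatement costs one paragraph and a less favourable power figure, and needs no further patients. If the sponsor wants to keep 90% with the unadjusted two-sided test and 20% withdrawal, the cost is 53–54 enrolled per group, which is 11–12 more in each.

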### Patients

2.4

Inclusion criteria:

1.All patients meet the diagnostic criteria of congenital heart disease-pulmonary hypertension (CHD-PAH),^[8]^ aged> 6 months and <16 years old;2.There is a risk of reactive pulmonary hypertension or pulmonary hypertension at the end of the operation Phenomenon;3.postoperative pulmonary artery systolic pressure/systemic arterial systolic pressure (Pp/Ps) ≥0.3, no decrease within 1 week;4.patients with moderate or higher pulmonary hypertension found in postoperative follow-up;5.preoperative pulmonary vascular resistance index (PVRI) ≥4 persons.

Exclusion criteria:

1.Children with other types of pulmonary hypertension related to non-congenital heart disease;2.Patients with liver and kidney dysfunction;3.Patients with prolonged QT syndrome;4.Patients concurrently using antiarrhythmic drugs;5.Allergic to test drugs;6.Severe digestive system or blood system abnormalities;7.Unable to understand after explanation.

The research protocol may be unwilling to participate.

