### Intervention

2.6

Control group: Oral vardenafil hydrochloride tablets, 20 mg/time, 1 time/d;

Treatment group: Oral bosentan tablets on the basis of the control group, according to the weight of the patient, weight <10 kg: 15.625 mg/time; weight: 10 to 20 kg: 31.25 mg/time; weight: 21 to 40 kg: 62.5 mg/time, 1 time/d.

The treatment lasts for 6 months. During the treatment period, the patients will be followed up by outpatient or telephone in the first and third months of treatment to understand the symptoms and adverse reactions of the patients, and review the observation indicators at the sixth month.

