### Observation index

2.7

1.Oxyhemoglobin saturation SpO2, using GEM3000 blood gas analyzer to measure SpO2 before and after treatment in the 2 groups;2.(2) 6-min walking test distance (6 MWTD): For children who can cooperate with walking to walk back and forth in a quiet and airy 30-m corridor, measure the 6-min walking distance;3.The patient uses a SwanGanz floating catheter for right heart catheterization in a resting state to determine systolic pulmonary artery pressure, pulmonary artery pressure, and aortic pressure. Fick method is used to calculate mean pulmonary artery pressure, pulmonary circulation blood flow quantity/systemic circulation Blood flow quantity, pulmonary artery systolic pressure/systemic artery systolic pressure;4.The patient got 5 ml of fasting venous blood in the morning before and after treatment, and the brain natriuretic peptide was measured by enzyme-linked immunosorbent assay;5.Borg score^[9]^ (divided into 0–10 grades, 10 is the most serious, consciously exhausted), cardiac function classification (NYHAFC);^[10]^6.Adverse reactions: including dizziness, headache, facial flushing, abnormal liver, and kidney function, etc.

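### Time from operation to enrolment is neither limited nor stratified, so early postoperative and later follow-up entrants may be mixed by chance, at a cost in precision rather than bias

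*Protocol article*

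**What the plan says.** Three items in section 2.4 (Patients) describe a child's state after surgery, each at a different time:

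- Item 2, at the close of surgery: "There is a risk of reactive pulmonary hypertension or pulmonary hypertension at the end of the operation".
- Item 3, about a week later: a pulmonary-to-systemic systolic pressure ratio of at least 0.3 with "no decrease within 1 week".
- Item 4, at an undated visit: "patients with moderate or higher pulmonary hypertension found in postoperative follow-up".

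The list has no connecting word to show whether a child must meet all the items or any one of items 2 to 5. It gives no minimum or maximum time from operation to enrolment.

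Section 2.5 (Study design) has participants "randomly assigned to the treatment group or control group at a ratio of 1:1" and says twice that there are no strata: "Randomization was performed without any stratification".

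Section 2.6 (Intervention) gives vardenafil to both arms, adds bosentan in one, treats for 6 months, and will "review the observation indicators at the sixth month". Section 2.7 (Observation index) words two indicators explicitly as before/after: SpO2 ("to measure SpO2 before and after treatment in the 2 groups") and brain natriuretic peptide ("The patient got 5 ml of fasting venous blood in the morning before and after treatment"). Section 2.9 (Statistical analysis) compares the groups, and the groups over time, by analysis of variance, and names no term for time since surgery. Among patient factors, the limitations paragraph in section 3 gives age as its only example.

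**The concern.** Suppose items 2 to 4 are separate routes into the trial. Some children would then have their baseline taken within about a week of heart surgery, and others at a follow-up visit that could be much later. A child just out of surgery can be expected to gain some walking distance, comfort and function over the next 6 months on either regimen. A child enrolled long afterwards has less of that recovery left. This is clinical reasoning; the article gives no figure for it.

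Time since operation is therefore plausibly prognostic for the outcomes. The plan neither restricts it, nor balances it, nor names it in the model. With 42 children per arm, simple randomisation can leave the arms noticeably different on such a factor, and unexplained spread from it lowers power. A later analysis plan could still add a covariate, but it cannot add a stratification factor or an entry window once enrolment is over.

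**Working it through.** **1. The plan's own figure.** Section 2.3 (Sample size) gives 6-minute walk means of 495.47 and 456.33 with SDs 54.72 and 54.68. The difference is δ = 39.14 m and the pooled SD is σ = √((54.72² + 54.68²)/2) = 54.70 m. The stated formula is n = 2(u_α + u_β)²σ²/δ².

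- One-sided 5%, 90% power: 2 × (1.645 + 1.282)² × 54.70² / 39.14² = 33.45, rounded up to 34. This reproduces the stated 34.
- Two-sided 5%, 90% power: 2 × (1.960 + 1.282)² × 54.70² / 39.14² = 41.04, rounded up to 42. This does not.

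Section 2.3 does not state sidedness, so both versions are shown below. The gap between them is a separate matter. No stated figure depends on time since surgery.

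**2. Effect of a mix on the SD (illustration).** The document does not give the following, so they are assumptions: half the children enter early; 54.7 m is the SD within each entry group; early and late entrants differ by D metres at the endpoint. With share p = 0.5,

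SD_mix = √(54.7² + p(1 − p)D²) = √(54.7² + D²/4).

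Power comes from the noncentral t distribution with 66 degrees of freedom and noncentrality 39.14 / (SD_mix × √(2/34)).

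| D (m) | SD_mix (m) | Noncentrality | Power, one-sided 5% | Power, two-sided 5% |
|---|---|---|---|---|
| 0 | 54.7 | 2.95 | 0.90 | 0.83 |
| 25 | 56.1 | 2.88 | 0.89 | 0.81 |
| 50 | 60.1 | 2.68 | 0.84 | 0.75 |
| 75 | 66.3 | 2.43 | 0.78 | 0.67 |

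**3. Chance imbalance.** Take two independent Binomial(42, 0.5) counts of early entrants. The probability that the arms differ by 8 or more is 0.101. That gap is 8/42 = 19 percentage points. With D = 50 m it moves the comparison by 0.19 × 50 = 9.5 m, or 9.5/39.14 = 24% of the planned difference. The standard error of the difference at 42 per arm is 54.7 × √(2/42) = 11.9 m, so the shift is 9.5/11.9 = 0.8 standard errors.

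**4. Steps 2 and 3 are one effect.** Random variation in the early share adds variance (D²/4)(2/n) to the mean difference. For D = 50 and n = 42 that is a standard deviation of √(625 × 2/42) = 5.5 m. Adding it to the 11.9 m gives √(11.9² + 5.5²) = 13.1 m, which equals 60.1 × √(2/42). The 9.5 m shift is one realisation of the spread already counted in the SD of 60.1 m. The two must not be added together.

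**The case against.** The case against has several parts, and most of it stands.

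- **No bias.** A reader might infer that surgical recovery distorts the estimated treatment effect. It does not do so systematically: both arms are drawn 1:1 from one pool and both receive vardenafil, so recovery is balanced in expectation. Chance imbalance is ordinary sampling error that the test already allows for, and unstratified randomisation is valid.
- **Pooling is inferred.** If every item had to be met, there would be no distinct early and late routes. The reading as alternatives is the more natural one, since item 2 admits mere risk while item 4 describes patients discovered at follow-up. The text does not settle it. Even under the cumulative reading, item 4 carries no time limit.
- **The size is assumed.** Neither the early share nor D is in the document. If early entrants catch up by month 6, D at the endpoint could be small. If the pre-test had the same mix, 54.7 m already contains the extra spread and nothing is lost; section 2.3 does not describe the pre-test population.
- **Within-arm change.** A reader might infer that the trial will present recovery as drug effect in before/after comparisons of every indicator. Section 2.9 plans comparisons between groups and between groups over time, not within-arm tests as the treatment effect, and only SpO2 and natriuretic peptide are worded as before/after.
- **Choice of factor.** Age, from 6 months to 16 years, is another candidate, and a condensed article may leave covariates and enrolment windows to the full protocol or analysis plan.

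What remains is that the article expressly rules out stratification, and its entry items run on different clocks with no stated way of combining them. Those are statements in the text, not omissions.

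**Conclusion.** The point holds as a matter of precision and clarity, not validity. Time from operation to enrolment is unrestricted, the way items 2 to 5 combine is unstated, and a plausibly prognostic factor is left to simple randomisation with 42 per arm. Under the illustrative assumptions (half early, 54.7 m within each entry group), the loss of power at 34 per group runs from about 1 point at D = 25 m to about 12 points at D = 75 m one-sided, and from about 2 to about 16 points two-sided. It is zero if the pre-test SD already covers the mix. These figures show a possible range and are not an estimate for this trial. This is a low-cost improvement worth making before enrolment; the documents do not show an error that invalidates the comparison.

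**What to change.** 1. In section 2.4, state whether items 2 to 5 are alternatives or must all be met.
2. Record the days from operation to randomisation for every child.
3. Add one two-level factor, early postoperative entry or entry at later follow-up, to the existing central randomisation, with a cut-off in days fixed before enrolment starts. Amend section 2.5 to match.
4. Include that factor in the between-group model in section 2.9.
5. In section 2.3, say whether the pre-test sample had the same mix of entry times, so that the SD of about 54.7 m can be judged.

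The cost is one extra field in the web randomisation, a slightly more complex allocation list and one degree of freedom in the model. No extra patients or visits are needed.
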